## Abstract

Research shows that exercise training programmes lead to several improvements in older adults’ health-related quality of life (HRQoL) and well-being. This study will examine the effects of an active retirement programme on Portuguese older adults, investigating its effects on body composition, physical fitness, HRQoL, and physical activity level (PAL). Therefore, a parallel-group randomised controlled trial will be conducted, including body composition (height and body weight), physical fitness (strength, flexibility, agility, postural control, and gait), HRQoL, and PAL assessments before and after the application of the programme. The programme will be carried out for six months, two days per week (45 min), plus a year of follow-up. The programme will consist of six circuits with eight physical exercises each. The circuits will change at the end of the four weeks (one monthly circuit). The exercises’ difficulty will increase throughout the programme, with alternatives for all the participants. If the effectiveness of the programme is demonstrated, implementation in different services and municipalities could be advised, as the actors involved in health and social services should promote the well-being of their citizens through, among others, health-related physical activity and the prevention of diseases associated with inactivity.

## 1. Introduction

Demographic ageing is the paradigm of the 21st century, and the older adult population is trending upwards. According to the central forecast scenario of the Office of Statistics National Institute, the number of older adults will increase from 2.1 to 2.8 million between 2015 and 2080 [1]. Thus, understanding and preventing disability in older adults is an important public health challenge, as ageing is a risk factor contributing to functional decline [2]. Ageing is continuous and irreversible and can be related to physical and cognitive function decline [3].

Physical activity (PA) plays an important role in healthy ageing, extending life, and quality of life, reducing chronic the incidence of physical and mental diseases. Moreover, every additional 15 min of daily PA (up to 100 min/day) reduces the mortality rate from any cause 4%. Although mechanisms underlying PA’s positive effects on health have not been fully revealed, evidence points to inflammatory markers, cellular oxidative stress regulation, and the impact on telomere length that could delay the ageing process [4]. According to the World Health Organization (WHO)’s recommendations [5], more than a quarter of the worldwide population (27.5%) does not perform at least 150 min of moderate or 75 min of vigorous PA per week [6]. Older adults should conduct, at least 150 min of moderate-intensity aerobics, at least 75 min of vigorous-intensity aerobics, or an equivalent combination of moderate- and vigorous-intensity PA throughout the week for substantial health benefits. Older adults should also perform moderate or greater-intensity muscle-strengthening activities that involve all major muscle groups two or more days a week, as these provide additional health benefits. As part of their weekly PA, older adults should practise multicomponent PA, emphasising functional balance and strength training at a moderate or high intensity three or more days a week to prevent falls [5]. In this sense, Gopinath et al. [4] carried out a study for 10 years in Australia, following up with adults over 50 years involved in moderate-vigorous PA (≥ 5000 MET minutes/week), which found that participants doubled their survival probability without chronic diseases, cognitive deficits, or functional incapacity. Moreover, PA levels (PAL) in older people should be higher than those recommended by the WHO (600 MET minutes/week) [5] to reach healthy ageing. There are 2.4 million individuals aged 65 and over in Portugal [7], with only 16.6% following the WHO’s recommendations [8]. A lack of PA contributes to the loss of functional fitness in the elderly [9]. Aerobic exercise is important for optimal musculoskeletal performance; however, aerobic capacity gradually declines with advancing age. Likewise, exercised muscles are more sensitive to anabolic stimuli, such as protein ingestion, which allow muscle protein synthesis [10]. As a result, sedentary elderly people have lower muscle mass and reduced bone mass, and, consequently, their ability to perform PA is affected.

Psychosocial factors also impact the functional status of the elderly. Self-efficacy and fear of falling are important factors [11]. Self-efficacy is not only associated with gait speed and physical-function limitations but also with participation in physical exercise programmes. In turn, fear of falling negatively influences sedentary behaviour time. Other psychosocial factors associated with reduced functional fitness are loneliness, depression, and exhaustion [10]. Moreover, physical factors impact the ageing process. A decrease in strength leads to a lower functional capacity, loss of balance, and decreased gait speed [12]: older adults generally have a wider gait, postural sway, and greater gait variability when walking [13]. Moreover, the sensorimotor system incorporates all processing and the afferent, efferent, and centrally integrating components involved in joints’ functional stability. As people age, this ability becomes limited, leading to important biomechanical changes in gait [14]. Loss of mobility, decreased muscle strength, and a balance deficit all contribute to dependence [15]. Hence, sensorimotor training improves older adults’ balance and provides gait confidence, although it does not affect the biomechanical parameters [16]. Several studies on sensorimotor training reported improvement in performance in clinical balance and mobility [17]: sensorimotor training-induced shortened onset latency in postural muscles [18], decreased onset latency, and enhanced reflex activity [19]. Sensorimotor training also induces an improvement in maximal and explosive-force production of leg extensors’ capacity [20] and improves lower-limb strength and power, static and dynamic balance, and mobility [21].

Research on how PA affects health-related quality of life (HRQoL) has shown that PA’s benefits regarding quality of life were limited [22,23]. Several studies have evaluated the sensorimotor system in the elderly and obtained strength, mobility, and balance improvements, but these results were not consistent due to the reduced sample [20,21], being short-term (12 weeks or less), or only assessing some abilities [17]. This study will last 24 weeks, and its effects will be measured through gait, postural control, strength, flexibility, balance, and agility. Hence, this study will aim to (1) assess the effectiveness of an active retirement programme on elderly body composition, physical fitness, HRQol, and PAL and (2) assess the programme’s effectiveness throughout the ageing process (follow-up).

## 2. Materials and Methods

### 2.1. Design

A parallel-group randomised controlled trial will be conducted, including a 6-month intervention phase and a 1-year follow-up period. For both groups (control and experimental), assessments will be performed at baseline (before starting the intervention), and after the intervention ends. The study will follow the Consolidated Standards of Reporting Trials Statement (CONSORT) [24].

### 2.2. Ethics

The Ethics Committee of the University of Évora approved this project (approval number: 21040). The study was registered with the Clinical Tri-als.gov PRS Protocol Registration and Results System (Registration Number: NCT05398354; https://www.clinicaltrials.gov/ct2/show/NCT05398354?term=NCT05398354&draw=2&rank=1 (accessed 12 June 2022).

### 2.3. Sample Size

Sample size calculations were performed using the G*Power 3.1.9.4 software (Kiel University, Kiel, Germany), selecting the statistical test to compare the difference between two independent means (two groups). Thus, accepting an alpha risk of 0.05 and a beta risk of 0.2 in a bilateral contrast and assuming a moderate effect size of 0.5, a total of 160 participants (80 subjects in the experimental group and 80 in the control group) were sufficient to reach a minimum potency of 90%.

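### The sample-size paragraph names two incompatible power targets (80% and at least 90%), and 160 participants follows directly from neither; the stated inputs give 88% with complete data

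*Protocol article*

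**What the plan says.** Section 2.3 (Sample Size) reports a G*Power calculation made by "selecting the statistical test to compare the difference between two independent means (two groups"). The inputs are given in one clause: "accepting an alpha risk of 0.05 and a beta risk of 0.2 in a bilateral contrast and assuming a moderate effect size of 0.5". The same sentence concludes that 160 participants, 80 in each group, "were sufficient to reach a minimum potency of 90"%. Section 2.4 (Randomisation and Blinding) fixes 1:1 allocation.

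Section 2.3 does not say whether 160 is the number to be recruited or the number to be analysed, and it states no allowance for losses. Section 2.1 (Design) describes a trial "including a 6-month intervention phase and a 1-year follow-up period", and section 2.7 (Measures) places an assessment one year after the intervention ends. Section 2.3 does not say which of these time points the calculation concerns.

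**The concern.** A beta risk of 0.2 means 80% power. A minimum power of 90% means a beta risk of at most 0.1. For one test, one effect size and one sample size, both cannot be the design target, and this conflict is visible before anything is calculated.

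The paragraph gives every input needed to recompute the sample size, so a reader can check whether 160 belongs to one target or the other. This is the article's only justification of the trial's size. If it stands, a result showing no difference could be presented as coming from a trial with at least 90% power for an effect of 0.5, which the stated calculation does not show. A reader also cannot tell how much room 160 leaves for losses.

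**Working it through.** **Inputs, all from the protocol article**
- Test: two independent means, two-sided, alpha 0.05 (section 2.3)
- Effect: d = 0.5 in standard-deviation units (section 2.3)
- Power: beta 0.2 (80%) and, separately, at least 90% (section 2.3)
- Size: 160 in total, 80 per group (section 2.3); allocation 1:1 (section 2.4)
- Loss: not given, so every loss rate below is an assumption

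**Method.** For n per group, the two-sample t-test has 2n − 2 degrees of freedom and noncentrality d × √(n/2). Power is the probability that a noncentral t variable with these parameters exceeds the two-sided 5% critical value in absolute size. The normal approximation n = 2(z₀.₉₇₅ + z_power)²/d² serves as a cross-check.

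**Step 1: power at the planned size.** With n = 80, the degrees of freedom are 158, the critical value is 1.975 and the noncentrality is 0.5 × √40 = 3.162. Power is 0.8816, or 88.2% (normal approximation 88.5%). The stated minimum of 90% is not reproduced; the gap is 90 − 88.2 = 1.8 points.

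**Step 2: size needed for each stated target.**

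| Target | Normal approximation, per group | Noncentral t, per group | Total | Compared with 160 |
|---|---|---|---|---|
| 80% (beta 0.2) | 2(1.960 + 0.842)²/0.25 = 62.8, so 63 | 63.77, so 64 | 128 | 128/160 = 0.80, 20% fewer |
| 90% (beta 0.1) | 2(1.960 + 1.282)²/0.25 = 84.1, so 85 | 85.03, so 86 | 172 | 172/160 = 1.075, 7.5% more |

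Neither target leads directly to 160.

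**Step 3: could another reading give 160 or 90%?**
- A one-sided test with 80 per group has 93.4% power, but the text specifies "in a bilateral contrast".
- If beta 0.2 is read as the tolerated limit and 90% as the power achieved, the power achieved is still 88.2%.
- Inflating the 80% result for 20% loss gives 128/(1 − 0.20) = 160 exactly. This fits the number, but the article states no such allowance, and under this reading the 90% figure is the mistake.

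**Step 4: sensitivity to loss (assumed rates, equal in both groups).**

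| Assumed loss | Analysed per group | Power |
|---|---|---|
| 0% | 80 | 88.2% |
| 5% | 76 | 86.5% |
| 10% | 72 | 84.6% |
| 15% | 68 | 82.5% |
| 20% | 64 | 80.1% |
| 25% | 60 | 77.5% |

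**Step 5: the planned adjusted analysis.** Section 2.8 (Statistical Analysis) plans an ANCOVA adjusted for age and baseline outcomes. If the baseline–outcome correlation is r, the effective standardised effect is approximately d/√(1 − r²). The article gives no r, so these values are assumptions. With 80 per group and no loss, power is 89.4% at r = 0.2, 90.1% at r = 0.25, 90.9% at r = 0.3 and 95.2% at r = 0.5. With 64 per group and r = 0.5 it is 89.99%.

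**The case against.** The strongest reply is that the error is small and that the trial may well be adequately powered. Much of this stands. With complete data the type II risk is 11.8% against the 10% implied by the 90% claim, and 80 per group has 90% power for d = 0.516, hardly different from the assumed 0.5. If 80% was the real target, 160 is more than enough and only the 90% figure is wrong.

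A reader might draw three stronger conclusions, which the document does not support:
- *The design cannot deliver 90% power.* What is shown is that the stated calculation does not give 90%. The baseline-adjusted analysis in section 2.8 could reach it with no loss at an assumed correlation of about 0.25. That does not repair section 2.3, which describes an unadjusted two-mean comparison and gives no correlation.
- *The real risk of missing the effect is about twice that stated.* This needs an assumed 20% loss and a comparison with the 90% claim only. At that loss the type II risk is 1 − 0.8015 = 0.1985, which is within the beta of 0.2 stated in the same sentence.
- *Losses over 18 months were ignored.* The article only fails to state an allowance. A condensed article may leave this to a fuller document, and 128/0.8 = 160 suggests that one was made. Nor does section 2.3 tie the calculation to the 18-month assessment.

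The contradiction within the sentence survives all of this, as does the fact that 90% is not a minimum for the calculation described.

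**Conclusion.** The point holds as an error in a stated design figure. Section 2.3 commits to both 80% and at least 90% power; the sample size follows directly from neither; and its own inputs give 88.2% with complete data. This conclusion rests only on figures in the article and on the test that it names.

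The size is modest: 1.8 percentage points with no loss. Any larger shortfall depends on loss rates that the article does not give, such as 80.1% power at an assumed 20% loss. The reading of 160 as 80% power plus a 20% allowance is plausible arithmetic but is not documented, and the sponsor would have to confirm it. This calls for a reporting correction and is not evidence of a design failure.

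**What to change.** Keep 160 participants and rewrite the sentence in section 2.3 so that it:
1. states one power target;
2. says whether 160 is the number recruited, including a loss allowance, or the number to be analysed;
3. replaces the 90% claim with a figure that the inputs support.

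Possible wording: *With 80 participants per group, a two-sided two-sample t-test at alpha 0.05 has 88% power to detect d = 0.5 if all are analysed, and about 80% if 20% are lost (assumed).* If the sponsor confirms that 160 came from inflating 128 for 20% loss, the sentence should say so and name 80% as the target.

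If the sponsor wishes to credit the planned baseline-adjusted ANCOVA, the paragraph should describe that calculation and state the assumed baseline–outcome correlation and its basis.

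The cost is one sentence. Enrolment, conduct and analysis do not change; the only consequence is that the reported unadjusted power becomes slightly less favourable.

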### 2.4. Randomisation and Blinding

Participants will be randomly assigned to the experimental (active retirement programme) or control groups. To assign participants to each group (1:1), Research Randomizer software (version 4.0, Geof-frey C. Urbaniak and Scott Plous, Middletown, CT, USA; http://www.randomizer.org, accessed 12 June 2022) will be used to create a randomisation sequence. A member of the research team, who will not participate in the intervention, will carry out this process. Group assignment will be hidden in a password-protected computer file. Participants will know their group assignment, but outcome assessors and data analysts will not know the participants’ group assignment.

### 2.5. Participants

Participants must meet the following inclusion criteria: (1) be retired; (2) be aged between 55 and 80; (3) show their agreement to participate in the study by providing a signed consent form; (4) be individuals without dentures (except dental prosthesis); and (4) not have undergone surgery for less than six months. Exclusion criteria will be individuals with (1) musculoskeletal diseases; (2) locomotion issues; (3) psychiatric disorders; (4) neurological disorders; and (5) cardiovascular diseases.

### 2.6. Intervention

**Experimental group:** This sensorimotor training programme will be carried out for six months, twice per week. As shown in Figure 1, as the programme progresses the load will be progressively increased.

Sessions will be divided into three intensity levels: easy (no external load during the first eight weeks), intermediate (application of external load: elastic bands, shin guards, and free weights, from the 9th week to the 16th week) and advanced (increase in external load for the previous level, from the 17th week to the 24th week). Each month, a different type of session will be developed (Figure 2). Each session will last 45 min and will be divided into three phases: an initial one, consisting of a 5 min walk followed by a joint warm-up (10 min); a fundamental phase (25 min), working on exercises circuits consisting of four cycles, with eight exercises each (50 s on and 15 s off); and a return to calm with muscle stretching (10 min). Additionally, at the end of every session, the intensity will be assessed using the Borg Rating of Perceived Exertion Scale, and the level of satisfaction of the participants will be assessed employing the Physical Activity Enjoyment Scale (PACES) [24].

**Control group:** Individuals will continue with their normal daily routine, only participating in the assessments. They will be offered to perform the exercise programme when the study ends.

Moreover, to guarantee participants’ safety, different strategies will be applied:-Anamnesis of all participants;-Hygiene of the material to be used during the sessions;-Breaks between exercises;-More than one researcher assisting with the sessions;-Application of the effort scale.

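### The circuit described in Section 2.6 takes 34.7 min (26.7 min of work even with no rests) but is placed in a 25 min phase, so at least one stated dose figure is wrong

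*Protocol article*

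**What the plan says.** All the figures are in the Intervention section (2.6) of the protocol article, in its description of a single session:

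- Session length: "Each session will last 45 min and will be divided into three phases".
- Initial phase: "consisting of a 5 min walk followed by a joint warm-up (10 min").
- Main phase: "a fundamental phase (25 min").
- Content of the main phase: "working on exercises circuits consisting of four cycles, with eight exercises each (50 s on and 15 s off").
- Closing phase: "a return to calm with muscle stretching (10 min").

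The same section lists "Breaks between exercises" among the measures that protect participants.

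The Abstract repeats two of these figures: the session length, in "two days per week (45 min"), and the number of exercises, in "The programme will consist of six circuits with eight physical exercises each". The four cycles, the 50 s, the 15 s and the 25 min each appear only once, in Section 2.6.

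**The concern.** One sentence fixes the length of the main phase and also everything needed to calculate that length, and the two do not agree.

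These figures define the dose of the trial's only intervention. An instructor following the text has to choose between stopping at 25 min with the circuit unfinished and completing four cycles in a session that overruns. Different instructors could choose differently. The adherence measures in Section 2.7 would not reveal this: they count completers, sessions attended, and weeks and days of exercise, but not cycles completed or minutes worked. The article also foresees use of the programme by other services and municipalities, and those users need a dose that can be delivered as described.

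**Working it through.** **Inputs (Section 2.6).** Cycles 4; exercises per cycle 8 (also in the Abstract); work 50 s; rest 15 s; main phase 25 min = 1,500 s; initial phase 10 min, taken to include the 5 min walk; closing phase 10 min; session 45 min (also in the Abstract).

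**Step 1. The plan's own total.** 10 + 25 + 10 = 45 min. The stated phase lengths reproduce the stated session length, provided the walk is inside the 10 min. The 25 min is therefore not an isolated slip: if it changes while the other phases stay as they are, the 45 min changes too.

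**Step 2. Duration of the circuit.** Duration = cycles × exercises × (work + rest) = 4 × 8 × (50 + 15) s = 2,080 s = 34.7 min. The excess is 34.7 − 25 = 9.7 min, and 9.67 / 25 = 39%.

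**Step 3. Could another reading give 25 min?**

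| Reading | Calculation | Duration |
|---|---|---|
| No rest after the final exercise | 32 × 50 + 31 × 15 = 2,065 s | 34.4 min |
| Rests within cycles only | 4 × (8 × 50 + 7 × 15) = 2,020 s | 33.7 min |
| No rests at all | 32 × 50 = 1,600 s | 26.7 min |
| Eight exercises in total, done once | 8 × 65 = 520 s | 8.7 min |

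None does. From the other direction, 1,500 s / 32 = 46.9 s is available per exercise including its rest, which is less than the 50 s of work alone. With the 15 s rest kept, 46.9 − 15 = 31.9 s remains for work.

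**Step 4. Session length as described.** 10 + 34.7 + 10 = 54.7 min, against 45 min stated. If the walk were additional to the 10 min, the stated phases would sum to 15 + 25 + 10 = 50 min, already inconsistent with 45 min, and the session as described would last 15 + 34.7 + 10 = 59.7 min.

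**Step 5. What the dose might be.** The three corrections below are illustrations; the article does not state the three cycles or the 30 s training interval. Sessions over the programme: 24 weeks × 2 = 48.

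| Correction | Main phase | Session | Work per session | Work over 48 sessions |
|---|---|---|---|---|
| (a) 3 cycles, 50/15 s | 3 × 8 × 65 = 1,560 s = 26.0 min | 46.0 min | 1,200 s = 20.0 min | 960 min |
| (b) 4 cycles, 30/15 s | 4 × 8 × 45 = 1,440 s = 24.0 min | 44.0 min | 960 s = 16.0 min | 768 min |
| (c) 4 cycles, 50/15 s | 2,080 s = 34.7 min | 54.7 min | 1,600 s = 26.7 min | 1,280 min |

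Without the rests at the end of each cycle, (a) takes 3 × (8 × 50 + 7 × 15) = 1,515 s = 25.25 min.

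**The case against.** The arithmetic is hard to dispute, but four things can be said on the other side.

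*The word cycles might mean something else.* The Abstract says circuits change monthly, so four cycles could mean four weekly cycles of one circuit, with the number of rounds per session left unstated. About three rounds at 50/15 s would then nearly fit. This reading is strained: the phrase sits in a sentence about the phases of one session, and three rounds is stated nowhere. It would also leave the sentence needing clarification.

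*Figure 2 covers the planning of the main part and is not available here.* It may show what is intended. That stands as a reason not to say which figure is wrong, but a figure cannot make the sentence in Section 2.6 add up.

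*The walk and the alternative doses are side points.* This largely stands. The 45 min total favours counting the walk within the 10 min, so the 50 and 59.7 min figures matter little. The range of 16.0 to 26.7 min of work comes from illustrative corrections; the size that rests on the document alone is 34.7 against 25 min.

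*The consequence is modest.* This also stands. Either the full circuit or a 25 min phase could be delivered, only not both. No harm to participants is shown, effort is rated at every session, and no estimate or test changes.

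**Conclusion.** The concern holds as stated. The figures for the main phase are mutually inconsistent by 9.7 min (39%) with rests and by 1.7 min (26.7 − 25) with none, so neither rounding nor the handling of rests explains the gap. The conclusion assumes only that the four cycles are rounds within one session, which is how the sentence reads. The 54.7 min session further assumes that the 10 min initial phase includes the walk.

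What is established is that at least one figure is wrong, not which one. The error should be corrected because it concerns the defining parameters of the intervention, but its reach is limited to how the dose is delivered, reported and replicated. Randomisation, the sample size and the analysis do not depend on it.

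**What to change.** Restate Section 2.6 with one set of figures that adds up, as the team intends and in agreement with Figure 2, keeping breaks between exercises. Say in the same place whether the 10 min initial phase includes the 5 min walk. Taking it as included, any of these would do:

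- (a) Three cycles at 50 s on and 15 s off, with the phase restated as about 26 min and the session as about 46 min.
- (b) Four cycles at about 30 s on and 15 s off (24.0 min), which fits the 25 min phase and 45 min session unchanged.
- (c) Four cycles at 50 s on and 15 s off, with the phase restated as about 35 min and the session as about 55 min.

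Under (a) or (c), change the 45 min in the Abstract as well. The cost is one to three numbers in Section 2.6, plus the one in the Abstract if the session length changes. Design, outcomes and analysis stay as they are.
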